## Abstract

**Background:**

Falls among older adults represent a major cause of morbidity and mortality, leading to decreased physical activity, loss of independence, and increased dependency. Individuals aged 60 years and older, particularly those with sensory deficits, are at greater risk. While conventional fall-prevention programs are widely implemented, innovative strategies such as active exergames have emerged as promising approaches to enhance balance and reduce fall risk.

**Objective:**

This study aims to evaluate the effectiveness of a supervised exergame-based multicomponent intervention compared to a traditional multicomponent training program in community-dwelling older adults at risk of falling.

**Methods:**

A randomized controlled trial with parallel groups and blinded assessment will be conducted among older adults (≥60 years) recruited from senior centers (SENAMA, Chile). Fifty-two participants will be randomly allocated to either an exergame group (n = 26), performing interactive full-body movements using the Nintendo Switch^®^, or a traditional multicomponent training group (n = 26). Both groups will receive 1-h supervised sessions twice weekly for 12 weeks. The primary outcomes will include fall risk, balance performance, functional independence and cardiorespiratory fitness. Secondary outcomes will assess body composition, muscular strength and quality, physical activity level, quality of life, and pain intensity and interference.

**Expected Results:**

It is hypothesized that both interventions will improve functional and balance outcomes, with the exergame-based program potentially promoting greater adherence and superior overall effects.

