### Power calculation

3.3

The sample size was calculated as *a priori* using G*Power 3.1.9.7. Forty-six participants in total are required (23 in each group), considering α = 0.05, 1-β = 0.8, and effect size (ES) = 0.8 (Lower limb strength based on the results of a previous study) Considering the possibility of dropouts percentage, six participants were added (see Figure 1).

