#### Primary outcomes

3.8.1

Risk of fall: Falls risk will be evaluated using the Downton Fall Risk Index (DFRI), a five-item composite score based on prior falls, medication, sensory deficits, mental state, and mobility. A score of less than three points means low risk of fall, and a total score above three points indicates a high risk of fall (Downton index, 2016).

Balance: Dynamic balance will be measured with the Timed Up and Go (TUG) test, which evaluates the time in seconds that a participant takes to rise from a chair, walk 3 m, turn, return, and sit down again (Mancilla et al., 2015) The test will be assessed three times, and the best attempt will be recorded. While static balance will be measured thought the single-Leg Stance Test, where participants must maintain balance on one leg for at least 5 s (Mancilla et al., 2015) The test will be assessed three times, and the best attempt will be recorded.

Posturography: Romberg quotient and C90 area will be measured (Smart Balance Hur® Labs model BTG4-F, Kokkola, Finland). Posturography records center of pressure displacement while standing on a stable platform (Furman, 1994; Visser et al., 2008). Participants must maintain a bipedal posture with feet shoulder width apart, hands hanging at the sides of the body and head facing forward. They must also follow the evaluator’s instruction, either eyes open (condition 1) or closed (condition 2). The foot resting points on the platform are marked to ensure repeatability.

Functional independence: this outcome will be measured with Functional Independence Measure (FIM) scale, it consists of 18 items that assess both motor and cognitive skills, and is scored on a 7-level scale, where one indicates total dependence and seven complete independence (Paolinelli et al., 2001).

Cardiorespiratory fitness: Aerobic capacity will be measured by the 2-Minute Walk Test, which measures the total distance (in meters) covered at a self-selected walking pace within 2 min on a flat surface, a full step is defined as a step performed by raising the knee to a height corresponding to the midpoint between the patella and the iliac crest (Guralnik et al., 1994).

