### Statistical analysis

3.10

Missing data will be handled by intention-to-treat analysis (multiple imputation method) [65]. The data will be analyzed using the intention-to-treat (ITT) strategy (Ahn and Kang, 2023). The description will be made as measures of central tendency and dispersion (continuous variables) and as percentages (categorical variables). Using the Shapiro-Wilk test, the normality of the data will be verified, and a two-step approach for transforming will be applied to the non-normal variables (A Two-Step Approach for Transforming, 2004). Homoscedasticity will be analyzed using Levene’s test. A 2-way repeated measures analysis of variance (ANOVA) will be used to determine the effects of interventions. The effects of the model are the group (GE; GC), the times (Pretest; Posttest), and their interaction over time (Time x Group). The effect size (ES) will be determined using Cohen’s d (<0.2 insignificant; ≥0.2 and ≤0.49 small; ≥0.5 and ≤0.79 moderate; ≥0.8 large) (Cohen, 2004). Additionally, in clinically relevant outcomes (risk of fall), the minimum clinically important difference (MCID) will be evaluated. All analyses will be performed with SPSS® v.26 (SPSS, Inc., Chicago, IL, USA), considering p < 0.05 and GraphPad Prism® v8.

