## Discussion

4

The primary objective of this study is to evaluate the effectiveness of a supervised exergame-based plus traditional multicomponent intervention compared to a traditional multicomponent training program in older adults at risk of falling. Based on the literature, it is hypothesized that both interventions will yield positive effects on primary and secondary outcomes. However, it is expected that the exergame-based program may result in equal or superior outcomes compared to the traditional intervention. This expectation is based on evidence suggesting that exergames can enhance exercise adherence and promote sustained engagement, which are often barriers in older adults (Valenzuela et al., 2018). Exergames have been described as an effective strategy to improve adherence to physical activity, particularly when integrated with social interaction and individualized support. Previous systematic reviews and meta-analyses have shown that exercise-based interventions benefit multiple domains of health in older adults, including functional capacity, balance, cardiorespiratory fitness, muscle strength, and quality of life, while also reducing fall risk (Fang et al., 2020; MacDermid et al., 2019; Ferreira et al., 2023; Ahn and Kang, 2023; A Two-Step Approach for Transforming, 2004; Cohen, 2004). These outcomes align with the anticipated benefits of both interventions in this study. However, while exergames show promise, there is limited evidence regarding their long-term impact on physical activity levels and fall prevention in older adults (Reis et al., 2019; Schoene et al., 2013). Additionally, exergames require specific equipment, and the cost of this technology remains a potential barrier for widespread implementation in day centers or community-based settings (Kari, 2014; Digitally, 2016).

While the potential benefits of incorporating exergames in elderly care settings are clear, challenges such as motivation to engage in physical activity, the perception of reduced social support when attending non-group-based interventions, and the financial cost of technological devices must be considered (Schürch et al., 2023). Despite these challenges, the personalized nature of the exergame-based program in this study, with direct supervision from trained professionals, is expected to mitigate some of these limitations by ensuring adherence to exercise guidelines and encouraging consistent engagement.

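### The hypothesis that both programmes improve outcomes rests on uncontrolled pre-post change and should be made descriptive; the randomised comparison is unaffected (minor)

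*Protocol article*

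**What the plan says.** The Abstract, under Expected Results, states: "It is hypothesized that both interventions will improve functional and balance outcomes". It adds that the exergame programme may do better. Section 4 (Discussion) widens the first part: "it is hypothesized that both interventions will yield positive effects on primary and secondary outcomes". It then expects the exergame arm to be equal or superior.

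The stated Objective in the Abstract is comparative: the exergame programme "compared to a traditional multicomponent training program in community-dwelling older adults at risk of falling". Section 2 (Aim), by contrast, speaks of effectiveness without naming a comparator.

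Both arms are trained: "Both groups will receive 1-h supervised sessions twice weekly for 12 weeks". Sections 3.6 and 3.8 describe one assessment before the programme and one after it.

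Section 3.10 gives a two-way repeated measures ANOVA the task of determining what the interventions do, at p < 0.05. On its terms it says: "The effects of the model are the group (GE; GC), the times (Pretest; Posttest), and their interaction over time (Time x Group"). It does not say which term decides the conclusion.

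For the Timed Up and Go and the single-leg stance, section 3.8.1 says: "The test will be assessed three times, and the best attempt will be recorded".

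**The concern.** The plan carries two hypotheses: that each programme works, and that one may work better than the other. Randomisation supports only the second. Group and Time x Group set one trained arm against the other, so neither says whether training improved anything. What remains for the first hypothesis is change from pretest to posttest, with nothing to compare it against.

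That change mixes any training effect with whatever else moves scores over about three months. The route best supported by the text is practice: the Timed Up and Go and the single-leg stance are performance tests, measured at a single baseline with the best attempt kept, and then repeated.

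At stake is one inference. If the interaction is null and Time is significant, the stated expectation of equal or superior results offers a ready reading, namely that both programmes work and work equally well. The design cannot support the first part of that reading. The mismatch lies between a hypothesis and a design that this document itself states, so it is not detail left to a separate analysis plan.

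**Working it through.** **Which term can bear on which claim**

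| Claim | Term in section 3.10 | Protected by randomisation? |
|---|---|---|
| Exergame arm differs from comparator | Time x Group | Yes |
| Both programmes improve outcomes | Time, or change within each arm | No: no untrained arm, no repeat baseline |

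This part needs no arithmetic. A significant pre-post change cannot be attributed to a programme, however often or rarely it would arise by drift.

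**How often drift alone would look like improvement**

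The plan has no figure of its own to reproduce here. The inputs are:

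- From the Abstract: "Fifty-two participants will be randomly allocated to either an exergame group (n = 26"), with 26 in the other arm, so N = 52.
- From section 3.10: p < 0.05, taken here as two-sided.
- Assumed, because the documents give neither: drift of 0.1, 0.2 or 0.3 baseline SD, the same in both arms, with no programme effect; and pre-post correlation r of 0.5 to 0.9, with equal SDs at both visits.

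Formulas:

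- SD of change = √(2(1 − r)) in baseline SD units, and dz = drift / SD of change.
- Pooled Time test: noncentral t, df = 50, noncentrality dz × √52, counting significant improvement.
- Both arms improve: paired t in each arm, df = 25, noncentrality dz × √26, and the probability squared because the arms are independent.

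Worked case, drift 0.2 SD and r = 0.7: SD of change = √0.6 = 0.775, and dz = 0.2 / 0.775 = 0.258. The pooled noncentrality is 0.258 × 7.211 = 1.86, which gives 45%. The per-arm noncentrality is 0.258 × 5.099 = 1.32, which gives about 24.5% per arm, and 0.245² = 6%.

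Each cell shows the pooled Time test, then both arms separately significant, for one outcome with no programme effect:

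| r | Drift 0.1 SD | Drift 0.2 SD | Drift 0.3 SD |
|---|---|---|---|
| 0.5 | 10.5% / 0.5% | 29% / 2.7% | 56% / 9.8% |
| 0.7 | 15% / 0.9% | 45% / 6% | 78% / 23% |
| 0.8 | 20% / 1.4% | 61% / 12% | 92% / 41% |
| 0.9 | 35% / 3.8% | 89% / 35% | 99.7% / 82% |

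With zero drift the rates are 2.5% and 0.1%.

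**Where the rate passes one half**

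- Pooled Time test: dz = 0.28, which is 0.22 baseline SD at r = 0.7 and 0.12 at r = 0.9.
- Both arms: dz = 0.51, which is 0.40 baseline SD at r = 0.7 and 0.23 at r = 0.9.
- If only the 46 of section 3.3 ("Forty-six participants in total are required (23 in each group") complete, the dz thresholds rise to 0.30 and 0.55.

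**More than one outcome**

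The plan does not say how many outcomes must improve. If any one of five sufficed (correlation 0.3 between outcomes, 5,000 simulated trials), the pooled Time test would confirm the hypothesis in 35%, 71% and 93% of trials at dz 0.1, 0.2 and 0.3. Requiring both arms to be significant on the same outcome gives 2%, 12% and 35%.

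**The case against.** The strongest reply is that the objective is comparative, that the sentence at issue sits under expected results and is introduced in the Discussion as drawn from the literature, and that no passage says a significant Time effect will be reported as proof that a programme works. This stands as far as it goes: misreporting is a risk the text leaves open, not something it commits to. It does not remove the point, because the hypothesis is stated twice, the model is meant to determine intervention effects, and nothing marks Time as descriptive.

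Four stronger readings are tempting, and the documents do not support them.

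- A reader might infer that drift would confirm the hypothesis most of the time. That depends on assumed drift and correlation. It also takes the pooled Time test as the criterion, although that test can be significant when only one arm changes. The hypothesis is about both arms, for which the rates are far lower.
- A reader might blame regression to the mean. Sections 3.4 and 3.5 select on no poor balance or fall-risk score. The cognitive and functional criteria are minimum scores, which would if anything lower the mean at retest.
- A reader might count the induction sessions as test familiarisation. Section 3.6 describes them as covering equipment and exergame use, not the outcome tests. Nor does best-of-three apply to every balance measure: no such rule is given for posturography.
- A reader might point to the day center's own services. Participants already attend the center, so these services are not stated to begin at baseline. Section 3.4 also excludes other exercise programmes.

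**Conclusion.** The concern holds in a limited form. The hypothesis that both programmes improve outcomes can be tested only by uncontrolled pre-post change, and neither programme's stand-alone efficacy can be concluded from it. This follows from the design and needs no assumed number.

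How often drift alone would mislead is unknown. For drift of 0.1 to 0.3 SD and correlation of 0.7 to 0.9, it runs from about 15% to nearly 100% for the pooled Time test. For both arms separately it is about 1% to 4% at 0.1 SD, 6% to 35% at 0.2 SD and 23% to 82% at 0.3 SD. All of these rest on equal drift in both arms, equal SDs at both visits and a two-sided 0.05 level.

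The Time x Group contrast, which answers the randomised question, is unaffected on this point. Severity is minor.

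**What to change.** In the Abstract (Expected Results) and section 4, limit the confirmatory hypothesis to the between-arm difference at 12 weeks.

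In section 3.10, add two statements:

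- Conclusions about effectiveness rest on the Time x Group (between-arm) contrast.
- Time and within-arm changes are descriptive, given as mean change with 95% CI, and are not evidence that either programme works on its own.

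The cost is wording only: the arms, sample size, outcomes and model stay as they are. The trial gives up the stand-alone efficacy claim for each programme, which this design cannot support.

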**Clinical Trial Registration:**

ClinicalTrials.gov. Identifier: NCT07024004.

## Introduction

1

The global population is aging rapidly, and the number of people aged 65 years and older is projected to more than double between 2020 and 2050, reaching approximately 16% of the world’s population (Rubenstein, 2006). Falls represent one of the leading causes of morbidity and mortality in this demographic, often resulting in mobility limitations, reduced quality of life, and loss of Independence (Rubenstein, 2006). Declines in lower-limb strength, impaired balance, and decreased functional mobility are key modifiable risk factors for falls (Pijnappels et al., 2008; Pijnap et al., 2008; Hamacher et al., 2018; Guideline for the prevention of falls in older persons. American Geriatrics Society, 2001). Targeted exercise interventions can mitigate these physiological declines by improving neuromuscular performance and thereby reducing the risk and incidence of falls (Shumway-Cook et al., 2007; Sherrington et al., 2011). Evidence supports the benefits of multicomponent exercise programs—including strength, balance, flexibility, and aerobic training—in maintaining functional capacity, preventing chronic diseases, and enhancing quality of life among older adults (Schneider et al., 2025; Li et al., 2025; Casas-Herrero et al., 2022). Such programs are most effective when they are personalized, supervised, and engaging, as these factors promote adherence and sustained participation (Reyna et al., 2020).

In recent years, technology-based exercise interventions have gained attention as innovative tools to increase motivation and long-term adherence among older adults. Exergames—interactive video games that combine exercise with virtual environments—offer a safe and enjoyable way to train balance, coordination, and strength (Valenzuela et al., 2018; Lee, 2013; Fang et al., 2020; Street et al., 2017). Research has shown that exergames can improve postural control, muscle strength, and functional independence in older adults and individuals with neurological conditions, while also enhancing psychological wellbeing and enjoyment compared to traditional exercise (Schroeder, 2008; Lavoie et al., 2025; Oh and Yang, 2010; Mejia-Downs et al., 2018; Bieryla and Dold, 2013; Rendon et al., 2012; O’Loughlin et al., 2020). Commercial platforms such as the Nintendo Wii®, Xbox Kinect®, and, more recently, the Ring Fit Adventure for Nintendo Switch® provide accessible options for such interventions (Li et al., 2018; Chua et al., 2013; Tanaka et al., 2012).

Despite these promising results, most studies to date have focused on short-term or unsupervised exergame interventions and have used heterogeneous technologies, making it difficult to determine which specific modalities or implementation strategies are most effective for fall prevention in older adults (Efficacy of Nintendo, 2018; Orsega-Smith et al., 2021). Furthermore, limited evidence exists comparing exergame-based programs integrated with multicomponent exercise against traditional exercise protocols under supervised conditions.

Therefore, this study aims to address this knowledge gap by evaluating the effectiveness of a supervised exergame-based multicomponent intervention compared with a traditional multicomponent training program in older adults at risk of falling. By combining evidence-based exercise principles with interactive digital technology, this study seeks to determine whether such integration can enhance adherence and yield superior improvements in balance, functional performance, and overall wellbeing.

## Aim

2

This study aims to evaluate the effectiveness of a supervised exergame-based multicomponent intervention on balance, cardiorespiratory fitness, muscle strength, and body composition in older adults at risk of falling. By providing context-specific evidence, this research seeks to determine whether integrating exergames into conventional training programs can enhance fall-prevention strategies and improve quality of life in this population.

## Methods

3

### Study design

3.1

This study is designed as a blinded (assessor and statistician), parallel group, randomized controlled trial (RCT). CONSORT guidelines for clinical trials will be followed (Hopewell et al., 2025), reporting on social and psychological interventions (Montgomery et al., 2018), and the SPIRIT guidelines for protocol studies (Chan et al., 2013) (Supplementary Table 1). The following ethical implications are considered: the signature of the informed consent of each subject before participation; voluntary participation; data will be handled anonymously; the private data of the participants will be anonymized, and we adhere to the international regulations on human research following the principles established in the Declaration of Helsinki (Serra, 2025). The protocol was submitted and approved to the ethical-scientific committee of Universidad Santo Tomás (Chile) (code n°238-MZS, Approval date 24 November 2024). In addition, the clinical trial was registered on ClinicalTrials.gov (ID: NCT07024004).

### Study setting and participants

3.2

National service for the elderly (SENAMA, in Spanish) in the Puente Alto district, metropolitan region, Santiago, Chile, will be invited to participate. SENAMA day center offers social and health services to the elderly during the day, with the aim of promoting their autonomy and independence, and preventing loss of functionality. These centers provide support through workshops and an individualized intervention plan, seeking to keep the elderly in their family and social environment. This day center was selected because it is the center that receives the largest number of elderly people in the metropolitan region. This provides access to a diverse group of older adults, including those who are frail and meet the study’s selection criteria. A collaboration agreement was created with SENAMA to be able to carry out outcome measurements and both protocols of exercise. In addition, this day center has a space equipped with a 50-inch smart TV and physical activity equipment so that a health professional can guide all the sessions.

### Power calculation

3.3

The sample size was calculated as *a priori* using G*Power 3.1.9.7. Forty-six participants in total are required (23 in each group), considering α = 0.05, 1-β = 0.8, and effect size (ES) = 0.8 (Lower limb strength based on the results of a previous study) Considering the possibility of dropouts percentage, six participants were added (see Figure 1).

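### The 46 participants (23 per group) in section 3.3 do not follow from its stated α, power and effect size under the usual two-group calculation

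*Protocol article*

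**What the plan says.** Section 3.3 (Power calculation) names the software, "The sample size was calculated as *a priori* using G*Power 3.1.9.7", and gives the inputs as "considering α = 0.05, 1-β = 0.8, and effect size (ES) = 0.8". The effect size is attributed to lower-limb strength in a previous study. The result is "Forty-six participants in total are required (23 in each group"), followed by "Considering the possibility of dropouts percentage, six participants were added". The Abstract randomises 52, 26 per arm.

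Section 3.3 does not name the test, the number of tails, the type of effect size or any correlation between repeated measurements. Section 3.10 (Statistical analysis) supplies some context: "The effect size (ES) will be determined using Cohen’s d", with values of 0.8 or more classed as large; the threshold is p < 0.05; and "A 2-way repeated measures analysis of variance (ANOVA) will be used to determine the effects of interventions", with group, time and their interaction as effects.

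**The concern.** Section 3.3 prints a full set of conventional inputs and an output, so a reader can check one against the other. For a two-group comparison of means they do not match, with either one or two tails.

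Two things depend on this. One is the claim of 80% power, against which a null result will be read. The other is the dropout allowance. If 46 completers are enough, the trial can lose six participants and keep its stated power. If 52 are needed, it can lose none.

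**Working it through.** **Inputs.** α = 0.05, power = 0.80, effect size 0.8, 23 per group, six added (all section 3.3); 26 per arm randomised (Abstract). Effect size read as Cohen's d (section 3.10). Test and tails are not stated, so both tails are tried.

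**The plan's own sum.** 46 + 6 = 52 = 2 × 26, and 6/52 = 11.5%. This part is consistent. The 46 is what needs checking.

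**Two-sample t test, equal arms.** With n per arm, the degrees of freedom are 2n − 2 and the noncentrality is d × √(n/2). Power is the probability that a noncentral t variable exceeds the critical value (in either direction for a two-sided test).

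At n = 23: noncentrality = 0.8 × √11.5 = 2.713, with 44 degrees of freedom. The two-sided critical value is 2.015 and power is 0.756. The one-sided critical value is 1.680 and power is 0.848.

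| n per arm | total | two-sided power | one-sided power |
|---|---|---|---|
| 20 | 40 | 0.693 | 0.799 |
| 21 | 42 | 0.716 | 0.817 |
| 23 | 46 | 0.756 | 0.848 |
| 25 | 50 | 0.791 | 0.874 |
| 26 | 52 | 0.807 | 0.885 |

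The smallest n reaching 0.80 is 26 per arm two-sided (52) or 21 per arm one-sided (42). The normal approximation, 2 × ((1.960 + 0.842)/0.8)² = 24.5, gives 25 per arm (50) two-sided and 20 per arm (40) one-sided. None of these is 46.

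**What would give 23 per arm.** Solving the two-sided calculation at n = 23 for 80% power gives d = 0.845. At n = 26 the same calculation gives d = 0.792.

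**Other routes tried.** All are totals at 80% power.
- Wilcoxon-Mann-Whitney, two-sided, normal parent: 54.
- ANCOVA with f = 0.4 (that is, d/2): 52.
- Repeated-measures ANOVA, f = 0.4, correlation 0.5: 16 for the interaction, 40 between groups.
- Repeated-measures ANOVA, f = 0.8, correlation 0.5: 6 to 12.
- Between-groups repeated-measures ANOVA, f = 0.4: 46, but only at a correlation of about 0.72 to 0.78.
- Baseline adjustment with a correlation of about 0.35: 46.

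The last two reach 46 only with a correlation that the article does not state.

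**The planned analysis.** With two time points, the Time × Group F test is the square of a t test on change scores. If 0.8 is in raw-score standard deviations and ρ is the pre-post correlation, the effective d on change is 0.8/√(2(1 − ρ)). The values of ρ are assumptions, since the article gives none. With 23 per arm, two-sided:

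| assumed ρ | effective d | power |
|---|---|---|
| 0.3 | 0.676 | 61% |
| 0.5 | 0.800 | 76% |
| 0.7 | 1.033 | 93% |

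If 0.8 is already in change-score standard deviations, power is 75.6% whatever ρ is.

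**The case against.** Four points can be made for the plan.

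1. **Section 3.3 names neither test nor tails, and a journal article often leaves software settings to the full protocol.** This stands in part. It rules out saying that the sponsor ran a two-sided t test and got it wrong. It does not remove the mismatch, because the printed inputs and output are offered as a complete statement and the usual readings do not connect them.

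2. **Rounding.** An effect size from 0.845 to just under 0.85 would print as 0.8 to one decimal and gives exactly 23 per arm, two-sided. This is possible, but the window is narrow and nothing in the article shows it. It is a good reason to ask for the unrounded value.

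3. **The planned test is a repeated-measures ANOVA, and one form of that calculation gives 46.** It does so only at an unstated correlation of about 0.72 to 0.78, and for the between-groups effect rather than the Time × Group interaction. So it shows only that other settings might explain the number.

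4. **The shortfall is small.** At d = 0.8 it is about 4 points (80% against 75.6%), and all 52 followed up would give 80.7%. This is correct. The intention-to-treat analysis with multiple imputation keeps all 52 in the analysis, but imputation does not restore the information lost with missing post-tests.

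A reader might infer that the trial is underpowered at 76%. The documents do not support that as a fact, because power for the planned interaction test at 46 completers runs from about 61% to 93% over assumed correlations of 0.3 to 0.7. A reader might also infer that enrolment must rise: 52/(1 − 6/52) = 58.8, so 59, or 60 for equal arms. That holds only if the two-sided t test was the basis and an 11.5% loss is a design assumption. The article fixes no dropout rate.

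**Conclusion.** The point holds as a failure to reproduce. With effect size read as Cohen's d, the stated α, power and effect size give 52 (two-sided) or 42 (one-sided), and 46 is neither. A one-sided test would make 46 more than enough (84.8%), but it would not have produced 46.

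Under the two-sided reading, which fits the F tests of section 3.10, 46 completers give 75.6% power. Type II error is then 24% rather than 20%, and the six participants added for dropout are already needed to reach 80%.

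This rests on three assumptions that section 3.3 does not confirm: a two-sided test, an independent t test, and d of exactly 0.8. Undisclosed settings may account for the figure. In either case section 3.3 does not support its power claim as written and needs correcting.

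**What to change.** Keep 52 randomised and rewrite section 3.3.

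- State the G*Power test, the tails, the unrounded effect size with its type, and any pre-post correlation entered.
- If it was a two-sided t test at d = 0.8, say that 52 completers (26 per arm) give 80.7% power and 46 give 75.6%, with a detectable d of about 0.845 at 80%. Stop describing the six as additional to the required number.
- If other settings produced 46, disclose them so that the figure can be reproduced.
- If power is claimed for the planned Time × Group test, state whether 0.8 is in raw-score or change-score standard deviations, the assumed pre-post correlation and the resulting power.

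The cost is one corrected paragraph. On the two-sided reading the stated power becomes slightly less favourable. Enrolment and the planned analysis do not change.
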